### Clinical outcomes

Patient reported outcome measures will be collected pre-operatively and 12-months post-operatively and include the Oxford Shoulder Score [32], Oxford Shoulder Instability Score [33], Disabilities of the Arm, Shoulder, and Hand Questionnaire Short Version (Quick DASH) [34], American Shoulder and Elbow Society Score [35], and the EQ-5D-5 L [36]. Standardised data collection will be overseen by the study’s research manager. Active range of movement of the affected shoulder will be assessed by the patient’s surgeon pre-operatively and 12-months postoperatively. To maximise follow up rates, assessment of 12-month outcomes will be aligned with the study centre’s registry research program which routinely collects 12-month postoperative data [37].

Outcome data will be summarised using means with standard deviations or medians with lower and upper quartiles if the data are skewed. Outcomes for AC and control participants will be compared pre-operatively and at 12 months using linear regression, adjusted for potential confounders such as age, employment status and dominant arm. Tests will be considered significant when *p* < 0.05. The limitations of comparing inherently different groups, for example with different pathology and treatment, will be recognised when interpreting the results.

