**Methods:**

The study is a prospective multi-centre longitudinal study investigating people undergoing arthroscopic capsulotomy for AC compared to people undergoing arthroscopic stabilization for shoulder instability. Tissue samples collected from the anterior glenohumeral joint capsule during surgery will undergo RNA-seq to determine differences in gene expression between the study groups. Gene Set Enrichment Analysis will be used to further understand the pathogenesis of AC as well as guide serum and urine biomarker analysis. Clinical outcomes regarding pain, function and quality of life will be assessed using the Oxford Shoulder Score, Oxford Shoulder Instability Score, Quick DASH, American Shoulder and Elbow Society Score, EQ-5D-5 L and active shoulder range of movement. Clinical outcomes will be collected pre-operatively and 12-months post-operatively and study groups will be compared for statistically significant differences using linear regression, adjusting for baseline demographic variables.

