## Background

Adhesive capsulitis (AC), or ‘frozen shoulder’ is a debilitating pathological condition of the glenohumeral joint, characterised by stiffness, pain and dysfunction [1, 2]. The condition is estimated to affect 2–5% of the general population, most commonly in women and people aged 40 to 60 years [3, 4]. The natural history of AC has been described as self-limiting, with resolution of symptoms within 2 years [5]. However, many people experience prolonged symptoms and functional limitations [6]. Hand et al. [7] found that 41% of 223 patients reported ongoing symptoms at 4 years following symptoms onset, with 6% still reporting severe pain and functional loss.

Diagnosing AC is usually based on clinical findings [6]. The American Shoulder and Elbow Surgeons consensus definition describes AC as “functional restriction of both active and passive shoulder motion for which radiographs of the glenohumeral joint are essentially unremarkable except for the possible presence of osteopenia or calcific tendonitis” [8]. However, in the absence of objective criteria, particularly in the early-stage AC [9], diagnosis can be contentious [10]. Patients usually report the onset of shoulder pain before loss of motion [11, 12]. External rotation is often the first reported movement restriction [1, 13], which is thought to be consequential to contraction of the coracohumeral ligament, one of the essential diagnostic findings in AC [1]. X-rays can be used to rule out other causes of shoulder pain and stiffness [14]. Ultrasound, magnetic resonance imaging (MRI) and magnetic resonance arthrography can detect features suggestive of AC such as capsular thickening, and loss of the inferior axillary pouch and joint volume [14]. Blood tests are usually normal, though cholesterol, triglycerides and C-reactive protein might be elevated in the early stages [10].

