### Study aims

The primary aim of the current study is to investigate gene expression alterations in people with primary and secondary AC compared to people with non-inflammatory shoulder instability (controls). Secondary aims are: 1) to interrogate gene expression data to identify potential serum and urine biomarkers that might assist in the early diagnosis and staging of AC; and 2) investigate clinical outcomes in people with AC compared to controls 12-months following arthroscopic capsular release or labral repair respectively.

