### Demographic data

At the pre-operative assessment, the following information will be collected from each participant: age, sex, employment status, dominant arm, symptom duration, employment status, type of work (e.g. heavy manual), prior treatment (e.g., physiotherapy, corticosteroid injection, hydrodilation), comorbidities and current medications.

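### The 12-month clinical comparison leaves out each outcome's own pre-operative score, so it carries forward any pre-operative gap, and no estimate of recovery is specified

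*Protocol article*

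**What the plan says.** The second secondary aim (protocol article, Study aims) is to "investigate clinical outcomes in people with AC compared to controls 12-months following arthroscopic capsular release or labral repair respectively".

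Under Clinical outcomes, "Patient reported outcome measures will be collected pre-operatively and 12-months post-operatively", and the surgeon measures active range of movement at the same two times. The analysis follows in one sentence: "Outcomes for AC and control participants will be compared pre-operatively and at 12 months using linear regression". That sentence goes on to describe the model for both time points as "adjusted for potential confounders such as age, employment status and dominant arm". The Methods paragraph of the abstract describes the adjustment as "using linear regression, adjusting for baseline demographic variables".

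The same section adds that the limits of comparing groups with different pathology and treatment will be recognised at interpretation. No change score, baseline-adjusted model or group-by-time term appears anywhere in the article.

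**The concern.** The two groups have different diseases and may start from different places on every scale. If so, a regression of the 12-month value on group and demographic covariates returns a mixture of the gap that existed before surgery and any difference in how the groups recovered. The article says that capsular release will be evaluated by comparison with the instability group, so readers will take the 12-month contrast as information about recovery. The measurement needed to separate the two parts is collected but is not given a role in the 12-month model.

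**Working it through.** **1. Is the pre-operative score in the model?** The covariate list is open-ended, so it has to be read with care. Two things point against the score being included. One list serves both the pre-operative and the 12-month comparison, and a pre-operative score cannot be a covariate in its own pre-operative comparison. The abstract also limits the adjusters to demographic variables, and the Demographic data section lists no outcome scores. The natural reading is two cross-sectional comparisons.

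**2. Is a baseline gap expected?** For active range of movement, yes. Under Eligibility criteria, the AC group must have lost more than 30% of active motion in every direction and at least 50% of external rotation. The comparison group has no such criterion. For the questionnaires the article gives no figures.

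**3. How large could the carry-over be?** There is no plan figure to reproduce, since no SD, effect size or power is stated.

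- From the article: n = 25 per group (Sample size) and significance at 0.05 (taken as two-sided).
- Assumed: standardised pre-operative gap D0 = 0.8; within-group pre-post correlation r = 0.3, 0.5 or 0.7; no group difference given baseline; complete follow-up; no other covariates.

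Expected 12-month gap = r × D0. Its standard error is √(2/25) = 0.283 SD. The chance of p < 0.05 is P(|Z + r·D0·√(25/2)| > 1.96).

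| r | 12-month gap (SD) | Shift in Z | Chance of p < 0.05 |
|---|---|---|---|
| 0.3 | 0.24 | 0.85 | 14% |
| 0.5 | 0.40 | 1.41 | 29% |
| 0.7 | 0.56 | 1.98 | 51% |

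Simulation with t-tests (20,000 runs per row) gives 13%, 28% and 49%. With the pre-operative score as a covariate, the rate is about 5% in each row.

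The result depends on the assumed gap. By the same formula, D0 = 0.5 gives about 8%, 14% and 24%, and D0 = 1.0 gives about 19%, 42% and 70%. With D0 = 0 there is no shift and the rate stays at 5%.

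**4. What does adjustment do to precision?** When the groups differ at baseline, group and score are correlated and part of the gain is lost. The variance of the adjusted difference is approximately (1 − r²) × (2/25 + D0²/48). At D0 = 0.8 the bracket is 0.0800 + 0.0133 = 0.0933. The equivalent unadjusted sample size per group is 2 divided by that variance.

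| r | Variance | SE (SD) | Equivalent n per group |
|---|---|---|---|
| 0.3 | 0.91 × 0.0933 = 0.0849 | 0.291 | 23.5 |
| 0.5 | 0.75 × 0.0933 = 0.0700 | 0.265 | 28.6 |
| 0.7 | 0.51 × 0.0933 = 0.0476 | 0.218 | 42.0 |

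Allowing for sampling variation in the observed gap, (0.64 + 0.08)/46 = 0.0157 replaces 0.0133, and the equivalents become 23.0, 27.9 and 41.0. Simulation agrees with these. So adjustment loses a little precision at r = 0.3 and gains at 0.5 and 0.7.

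**5. Does baseline adjustment give the one right answer?** No. If both groups improve by the same mean amount, the 12-month gap stays at D0 and the baseline-adjusted difference is D0 × (1 − r), which is 0.8 × 0.5 = 0.40 SD at r = 0.5. Conversely, if there is no difference given baseline, the difference in mean change is −D0 × (1 − r), of the same size. The two estimates answer different questions.

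**The case against.** The strongest reply is that the stated aim is outcomes at 12 months. If the 12-month difference is itself the target, a carried-over gap is a real difference and detecting it is no error. This stands as a limit on the percentages: they are false-positive rates only under a null of no difference given baseline, and only for the assumed inputs and a test without covariates. It does not supply an estimate of recovery.

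A second reply is that the article reports the pre-operative comparison and promises caution over unlike groups. That tempers the reading but does not change the estimate. It does mean that a reader should not say that the plan presents pre-operative gaps as effects of surgery.

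A third reply is that a journal article may leave the exact covariate list and the tables of change to a fuller document. That would excuse silence, but here the model is stated twice, in terms that do not naturally reach an outcome score.

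Three stronger readings are tempting and are not supported:

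- **Sex is omitted.** It is not among the named examples, but Demographic data lists "age, sex, employment status, dominant arm, symptom duration", so it falls within the abstract's wording. The Background says AC occurs "most commonly in women and people aged 40 to 60 years", but the article gives no sex mix for the instability group. Naming sex would be a clarification only.
- **Recovery will be judged by setting one p-value against the other.** Nothing in the article says so.
- **Precision is simply thrown away.** At low correlation with a wide baseline gap, adjustment costs a little precision.

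**Conclusion.** The point holds in limited form. As described, the 12-month model omits the same outcome's pre-operative value, so its group contrast includes whatever part of the pre-operative gap persists. For active range of movement that gap follows from the eligibility rule; for the questionnaires it is plausible but unquantified. No estimate of recovery is specified. The illustrative size, 14% to 51% positive tests instead of 5%, rests on an assumed 0.8 SD gap, assumed correlations of 0.3 to 0.7, a null conditional on baseline and a test without covariates. It shows how the carry-over behaves and does not predict this study's error rate. A reader might infer that baseline adjustment would make the groups comparable. It would not: they are not randomised, and no analysis here separates disease from operation. The primary gene-expression aim is unaffected.

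**What to change.** Under Clinical outcomes, state that each 12-month regression includes the pre-operative score of the same outcome alongside the chosen covariates. Report mean change within each group with a 95% confidence interval, and the between-group difference in change beside the baseline-adjusted estimate. Say that the two can differ in non-randomised groups and that neither separates disease from operation. Bring the abstract's wording into line. If the covariate list is being edited anyway, fix it, keep it short for 50 participants and name sex.

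The cost is a sentence or two and one more degree of freedom per model, with no new data. The possible downside is the small loss of precision shown above: with a 0.8 SD gap, 25 per group would act like about 23 at correlation 0.3, against about 28 at 0.5 and 41 to 42 at 0.7.

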### Demographic data

At the pre-operative assessment, the following information will be collected from each participant: age, sex, employment status, dominant arm, symptom duration, employment status, type of work (e.g. heavy manual), prior treatment (e.g., physiotherapy, corticosteroid injection, hydrodilation), comorbidities and current medications.

### Data management and blinding

Research personnel will keep records of sample collection and processing times, and enter clinical data into REDCap [38], a password-protected electronic data collection and management tool hosted at Barwon Health.

Personnel assessing tissue samples will be blinded to the study group. Functional outcome scores will be collected independent of surgeons; however, surgeons will collect shoulder active range of movement scores.

### Sample size

The majority of the molecular parameters being compared in this study are new in this disease setting and few datasets exist from which to estimate the sample size. Hagiwara et al. [21] found significant differences in gene expression for 33 genes with 12 AC and 18 control samples. To increase the likelihood of detecting differences in gene expression between our groups, we plan to recruit 25 participants per group. This sample size represents a pragmatic decision, based on our expectation of being able to recruit 50 participants over a two-year period, and our desire to increase the statistical power of our study compared to other research.

## Discussion

The current study will fill a knowledge gap and provide much needed empirical evidence regarding the pathogenesis of AC. The results may be used to develop more effective methods to diagnose and treat AC.

## Abbreviations

AC: Adhesive capsulitis
MRI: Magnetic resonance imaging
